#### Interim analyses {21b}

No formal interim analyses are planned; however, the Data and Safety Monitoring Committee (DSMC) will be charged with advising the Management Committee of the need to update the trial design or terminate the trial early based on clear evidence of harm or efficacy prior to scheduled completion.

#### **Methods for additional analyses (e.g. subgroup analyses) {20b}**

Subgroup analyses will consider the effect of age, sex, recruitment country, smoking, coronary heart disease, peripheral artery disease, initial AAA diameter and HbA1c on the primary outcome.

#### **Methods in analysis to handle protocol non-adherence and any statistical methods to handle missing data {20c}**

A per-protocol analysis is planned focused on participants who regularly took the study drug every day or nearly every day.

#### **Plans to give access to the full protocol, participant-level data and statistical code {31c}**

It is envisaged that the datasets analysed during the current study will be available from the corresponding author on reasonable request although approval for this has not been obtained at this point.

### Oversight and monitoring

#### Composition of the coordinating centre and trial steering committee {5d}

MAT is an investigator-initiated and investigator-conducted study. MAT is managed by a Central Coordinating Centre based at the Queensland Research Centre for Peripheral Vascular Disease (QRC-PVD) at James Cook University in Townsville, Australia, and supported by The George Institute for Global Health in Sydney, Australia. The study is overseen by a Steering Committee (SC) comprised of experienced investigators, healthcare providers, statisticians, trialists and epidemiologists with appropriate clinical and research expertise relevant to the design and conduct of MAT. The steering committee is responsible for the execution of the study design, protocol, data collection and analysis plan, as well as publications. The SC has the right to appoint new members and co-opt others to add to the integrity of the conduct of the study and analyses. The SC is co-chaired by [name] and [name].

#### Composition of the data monitoring committee, its role and reporting structure {21a}

The DSMC will monitor safety outcomes for potential harmful effects and provide reports to the SC on recommendations to continue, modify or halt the study. The DSMC will be governed by a charter that will outline their responsibilities, procedures and confidentiality. They will review unblinded data from the study at regular intervals during follow-up. The first meeting will be held within 6 months after the start of recruitment.

### Adverse event reporting and harms {22}

#### Adverse events (AE)

An AE is defined as any untoward medical occurrence in a patient or clinical investigation subject administered a pharmaceutical product at any dose and which does not necessarily have a causal relationship with this treatment. Therefore, an AE can be any unfavourable and unintended sign (including an abnormal laboratory finding, for example), symptom or disease temporarily associated with the use of an investigational product. This definition includes intercurrent illness or injuries and an exacerbation of a pre-existing condition.

#### Adverse events of special interest (AESI)

Since the safety profile of metformin is well established, only adverse events of special interest (AESI) will be collected during the course of the MAT study. This will include symptomatic hypoglycaemia and lactic acidosis.

#### Serious adverse events (SAEs)

A SAE is defined as any untoward medical occurrence that at any dose:
Results in deathIs life-threatening in the opinion of the attending clinician (i.e. the patient was at risk of death at the time of the event; it does not refer to an event that might hypothetically have caused death if it had been more severe)Requires inpatient hospital admission or prolongation of existing hospital stay. Any hospital admission that was planned prior to randomisation will not be reported as an SAEResults in persistent or significant disability or incapacityResults in congenital anomaly or birth defectIs an important medical event in the opinion of the attending clinician (i.e. not life-threatening or resulting in hospital admission, but may jeopardise the participant or require intervention to prevent one or other of the outcomes listed above)

All SAEs are required to be reported via the Web-based data management system within 24 h of the study team first becoming aware of the event by reporting the event in the eCRF. SAEs are also required to be reported to the site investigator and to the relevant EC/IRB and/or sponsor in accordance with and within the timeframes specified in the relevant committee guidelines.

AEs that do not fall into these categories are defined as non-serious. If treatment is discontinued as a result of any AE, serious or non-serious, the study team will document all events leading to the discontinuation of treatment. SAEs will be collected from the time a participant gives written consent until completion of the study. If an SAE is unresolved at the conclusion of the study or if the participant withdraws early from the study, a clinical assessment will be made by the investigator as to whether continued follow-up of the SAE is warranted.

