### Outcomes {12}

#### Primary outcome

The primary assessment will compare the number of AAA events (defined as the occurrence of AAA repair or AAA mortality due to rupture) between study groups which were observed during the treatment period. This will be in the form of an intention to treat (ITT) comparison including all randomised participants.

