#### Safety assessments

Safety assessments will be performed on the per-protocol and ITT datasets of the effects of allocation to metformin versus placebo during the study period on:
iTotal serious adverse eventsiiLactic acidosisiiiSymptomatic hypoglycaemia

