### Participant timeline {13}

A summary of all study assessments is presented in Table 1.

**Table 1 Tab1:** Schedule of evaluations

Visit	Screening −10 to −6 weeks	Run-in^**a**^ −6 to 0 weeks	Randomisation 0 weeks	Follow-up^**b**^			
				3 monthly	6 monthly	Annually	Final^**c**^
Time window for evaluation	N/A	+ 2 days	N/A	±14 days	±14 days	±14 days	N/A^c^
Informed consent (prior to or at screening)	X						
Assessment of eligibility	X						
Demographics	X						
Anthropometrics—height and weight	X					X^f^	X^f^
Behavioural—smoking	X						
Medical history	X						
Concomitant medications	X					X	X
AAA imaging (standard care)^h^	X					X	X
Blood tests—creatinine, eGFR, HbA1c, CRP (if available), LDL-C (if available)^d^	X					X^g^	X^g^
Blood sample for biomarker sub-study^e^	X					X^e^	X
QoL questionnaires: SF-36, AneurysmDQoL	X					X	X
Run-in medication dispensed	X						
Randomisation			X				
Study medication dispensed			X		X	X	
Study medication adherence		X		X	X	X	X
AESI reporting		X		X	X	X	X
Serious adverse event reporting		X		X	X	X	X
Assessment of exploratory outcomes not classified as SAEs (diagnosis of cancer, diagnosis of diabetes, symptomatic gout)				X	X	X	X
Health economic assessment questions						X	X

^a^Participants will be contacted by telephone fortnightly during the 6-week run-in period

^b^Participants will be contacted every 3 months after randomisation

^c^Participants will undergo a final follow-up within 3 months of the date of the last adjudicated primary outcome event

^d^If blood tests are available from within 6 months prior to screening, no need to repeat tests at screening

^e^Only for participants who have consented to the biomarker sub-study. Samples will be collected at entry, at years 1 and 3, and at the final scheduled follow-up

^f^Weight only

^g^eGFR only. If blood tests are available from within 3 months prior to annual follow-up/final follow-up, no need to repeat tests

^h^If imaging is available within 12 months of screening/annual follow-up, no need to repeat tests

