### Sample size {14}

While the trial is outcome event driven (an estimated 616 primary outcome events are needed), a sample size estimate has considered the likely participant numbers needed. The planned sample size is 1954 (metformin *n* = 977; placebo *n* = 977) which will provide 90% power (*p* = 0.05) to detect a 25% or greater reduction in the relative risk of the primary outcome with metformin compared to placebo over a mean follow-up of 3.5 years. This calculation was based on:
A 25% relative risk reduction for the primary outcome which is less than reported by observational studies comparing AAA events between patients who were, or were not receiving metformin [42]An AAA repair or rupture rate of 9% per annum (31% over 3.5 years) in the control group has been assumed to accrue a total of 616 primary endpoint events in the trial. This event rate is lower than the occurrence of AAA repair or rupture in our prospective registry (AAA events observed at 12% per annum) [42] and less than that reported in a number of small AAA trials [2, 43]. For example, the UK small aneurysm trial and the surveillance versus aortic endografting for small aneurysm (CAESAR) trial reported 3-year rates of AAA rupture or repair of 52% and 61%, respectively [43]A drop-out rate of 5% per annum (discontinuation of metformin in the intervention group) which is expected to be minimised by the active run-in periodA drop-in rate of 1% per annum (commencement of metformin in the control group) which is expected to be low because incident diabetes will be uncommon and options for use of therapy based on agents other than metformin will be discussed with participants and their responsible physician

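### The SAE definition takes in AAA repairs and rupture deaths, so comparing arms on total SAEs mixes efficacy with harm and can partly mask an excess of other serious events

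*Protocol article*

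**What the plan says.** **Safety outcomes.** Under Safety assessments the article states: "Safety assessments will be performed on the per-protocol and ITT datasets". It lists three outcomes: total SAEs, lactic acidosis and symptomatic hypoglycaemia. Only the first is not tied to a single condition.

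**Definitions.** An adverse event includes "an exacerbation of a pre-existing condition". It becomes serious if it results in death or meets another listed criterion. The criterion that matters here, together with the one exemption, covers inpatient "hospital admission or prolongation of existing hospital stay. Any hospital admission that was planned prior to randomisation will not be reported" as an SAE. The inclusion criteria admit only patients whose treating doctor has no current plan for repair, so that exemption should rarely remove an on-trial AAA repair.

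**Primary outcome.** It is "the occurrence of AAA repair or AAA mortality due to rupture". All potential primary events are adjudicated blind (Adjudication). Nothing in the article takes them out of the SAE count, and no SAE comparison without them is described.

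**Planning figures.** Sample size {14} assumes "An AAA repair or rupture rate of 9% per annum (31% over 3.5 years) in the control group", a 25% relative reduction, 977 participants per arm and a mean follow-up of 3.5 years.

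**The concern.** A count that includes the efficacy endpoint falls when the drug works. If metformin prevents repairs, total SAEs drop on metformin for that reason alone, and an excess of unrelated serious admissions has to exceed the drop before it shows. Similar SAE totals are easily read as evidence of safety; the Discussion cites similar SAE rates in an earlier placebo-controlled metformin trial in just that way. In this trial, level totals could mean no harm, or they could mean a benefit on the aneurysm offset by harm elsewhere. The total alone cannot tell these apart.

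**Working it through.** **Inputs from the article (Sample size {14}).** Control risk 9% per annum, 31% over 3.5 years; relative reduction 25%; 977 per arm; drop-out 5% and drop-in 1% per annum; 616 events planned.

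**The plan's own figures.** 0.09 × 3.5 = 0.315, the stated 31%. For a hazard ratio of 0.75, two-sided 5% alpha and 90% power, the Schoenfeld formula gives 4(1.960 + 1.282)² / (ln 0.75)² = 508 events. Inflating for 17.5% drop-out gives 508 / 0.825 = 615.8, which reproduces 616. The article does not show its derivation; 0.315 × 1954 = 615.5 reaches the same number.

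**Step 1: SAEs removed by efficacy alone**, counting one SAE per AAA event.
- Placebo: 0.31 × 977 = 303. Metformin: 303 × 0.75 = 227. Difference: 76.
- Upper end: 0.315 × 977 × 0.25 = 77.
- Lower end: compound the control risk, 1 − exp(−0.315) = 0.270, and dilute the effect for drop-out and drop-in at mid-follow-up, 0.25 × (1 − 0.06 × 1.75) = 0.224, a ratio of 0.776. Then 0.270 × 977 × 0.224 = 59.

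**Step 2: the excess that this hides.** Person-years per arm: 977 × 3.5 = 3,419.5. The article gives no rate for non-AAA SAEs, so three rates are assumed. The hidden rate ratio is 1 + (SAEs removed) / (control non-AAA SAEs). The z statistic is the log rate ratio divided by √(1/a + 1/b), where a and b are the counts in the two arms.

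| Assumed non-AAA SAEs per 100 person-years | Control count | Rate ratio hidden by 76 | Range for 59 to 77 | z, AAA events left out | z, total SAEs |
|---|---|---|---|---|---|
| 5 | 171 | 1.44 | 1.35–1.45 | 3.70 | 0 |
| 10 | 342 | 1.22 | 1.17–1.23 | 2.75 | 0 |
| 20 | 684 | 1.11 | 1.09–1.11 | 2.00 | 0 |

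**Step 3: a worked case.** Take 10 per 100 person-years and a true 20% excess of other SAEs on metformin. Without AAA events the counts are 410 against 342, z = 2.5. With them they are 410 + 227 = 637 against 342 + 303 = 645, a ratio of 0.99 and z = −0.2.

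**Step 4: participants instead of events.** The article does not say which it will count. For participants with at least one SAE, assuming independent risks, the AAA hazards over 3.5 years are −ln(0.69) = 0.371 and −ln(0.7675) = 0.265. The gap of about 0.106, divided by background hazards of 0.175, 0.35 and 0.70, gives hidden hazard ratios of 1.61, 1.30 and 1.15. Masking is no weaker on this scale.

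The z values treat SAEs as independent Poisson counts. Repeat SAEs in one person would shrink them, but would not change the counts needed to level the totals.

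**The case against.** **The analysis plan may deal with it.** How SAE tables are broken down is usually left to the SAP, and the article says it gives only a brief account of methods. It rules out no further breakdown, and a SAP that is not shown may contain one. This limits the force of the point. It does not remove it, because the article itself names the outcome as total SAEs and defines SAEs with a single exemption that does not reach the primary outcome. Followed as written, the two are pooled.

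**Other data would show much of the harm.** This stands. All-cause mortality, MACE and peripheral vascular procedures are secondary outcomes; cause-specific death and cancer are exploratory outcomes; lactic acidosis and hypoglycaemia are reported apart; and events leading to discontinuation, serious or not, are documented. A reader might infer that total SAEs are the main safety outcome, or the only broad view of harm. The article ranks nothing among its safety outcomes, and these other sources narrow the exposed area to other non-fatal serious admissions.

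**The monitoring committee is not blind to the mix.** It reviews unblinded data at regular intervals, and nothing says that it sees only a pooled total. A reader might infer that the committee would be misled; the article does not support that.

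**Classification of repairs is inferred.** The Table 1 row headed "Assessment of exploratory outcomes not classified as SAEs" may look like confirmation that repairs are SAEs. It covers only cancer, diabetes and gout and is silent on primary events. Nor does the article say that every repair is an SAE: the repair must be inpatient and be reported as an untoward occurrence. If sites differ on that, the total becomes inconsistent as well as mixed.

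**Counting every serious event by arm is legitimate.** This also stands, and is a reason to keep the total. Leaving out whole repair admissions would discard complications that may themselves be harm.

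**Conclusion.** The point holds in a limited form. As the article defines its terms, post-randomisation AAA repairs (if inpatient and reported as untoward) and rupture deaths enter the total SAE comparison. If metformin achieves the planned effect, about 59 to 77 fewer SAEs on metformin would reflect efficacy alone over 3.5 years, and an excess of other serious events of that size would be invisible in the total. As a rate ratio this is about 1.4, 1.2 or 1.1 at assumed background rates of 5, 10 or 20 per 100 person-years. Those rates are assumptions, so no single masked percentage should be quoted as a property of this trial. The masking shrinks in proportion if the benefit is smaller and vanishes if there is none. It is partial, because most major categories of harm are captured elsewhere. It is worth correcting because the correction needs no new data.

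**What to change.** In Safety assessments, keep total SAEs and add one pre-specified comparison: SAEs excluding adjudicated primary-outcome events, meaning the AAA repair or rupture death itself. Complications that arise during those admissions should still be counted. State whether each comparison counts events or participants, and show both lines in the monitoring committee's reports. SAE collection and expedited reporting stay as they are.

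The cost is a sentence or two and one extra table row. Blind adjudication already identifies the events to be left out. The change should be fixed before unblinding.

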#### Suspected unexpected serious adverse reactions (SUSAR)

An unexpected adverse reaction (UAR) is an adverse reaction, the nature or severity of which is not consistent with the applicable product information. A SUSAR is any UAR that at any dose meets the definition of an SAE. All SUSARs will be reported to regulatory authorities in accordance with country-specific requirements and in compliance with *International Council on Harmonisation* (*ICH*) *Clinical Safety Data Management: Definitions and Standards for Expedited Reporting*.

### Frequency and plans for auditing trial conduct {23}

Prior to commencement of the study at any participating centre, all designated research staff including the PI, co-investigator(s) and research nurse(s)/coordinator(s) will be trained in the study procedures. Data monitoring will take a risk-based approach and involve a combination of remote, online and on-site monitoring. At least once per year, representatives of the coordinating centre will conduct a monitoring visit to all participating centres by video-conference, or if feasible or required on-site visits will take place. Study monitoring will ensure that the study is being conducted in accordance with the protocol, ICH GCP Guidelines, and meets relevant ethical and regulatory requirements. The monitor will verify patient consent and eligibility and review relevant source documents according to a detailed monitoring plan available as a separate document. At completion of the study, the monitor will ensure that there are plans in place for the long-term storage of all the relevant data and source documentation (for a minimum of 15 years or a longer period if required by applicable regulatory requirements). The study may be audited by third parties and inspected by government regulatory authorities. CRFs, source documents and other study files must be accessible at all study sites at the time of auditing and inspection during the course of the study and after completion of the study.

### Plans for communicating important protocol amendments to relevant parties (e.g. trial participants, ethical committees) {25}

This study will be carried out according to ICH GCP Guidelines, the NHMRC National Statement on Ethical Conduct in Research Involving Humans (1999) and the Notes for Guidance on Good Clinical Practice as adopted by the Therapeutic Goods Administration (2000) (CPMP/ICH/135/95), applicable local regulations including the EU Clinical Trial regulation and with the ethical principles laid down in the World Medical Associations Declaration of Helsinki. The protocol, PISCF, any material to be given to prospective participants and any subsequent modifications will be reviewed and approved by the EC or IRB responsible for oversight of the study. Prior to study commencement, investigators are required to sign a protocol signature page confirming his/her agreement to conduct the study in accordance with these documents and all the instructions and procedures contained in this protocol and to give access to all relevant data and records to monitors, auditors, IRB/ECs and regulatory authorities as required. If an inspection of the clinical site is requested by a regulatory authority, the investigator must inform the coordinating centre immediately.

An amendment is defined as a written description of change(s) to or formal clarification of a study protocol which may impact the conduct of the clinical study, potential benefit of the clinical study, or may affect subject safety, including changes of study objectives, study design, subject population, sample size, study procedures or significant administrative aspects. An administrative change is defined as a minor correction or clarification that has no significant impact on the way the clinical study is conducted and no effect on subject safety. Protocol amendments must be approved by the Steering Committee, Regulatory Authorities where required and the EC/IRB. In cases where the amendment is required in order to protect the subject safety, the amendment can be implemented prior to the EC/IRB approval. Notwithstanding the need for formal approval of a protocol amendment, the investigator is expected to take any immediate action required for the safety of any subject included in the study, even if this action represents a deviation from the protocol. In such cases, the coordinating centre should be notified of this action and the relevant EC/IRB informed within 72 h.

### Dissemination plans {31a}

The study protocol and results of this study will be published in peer-reviewed journals and made available to all participants, investigators and the research community. The study protocol and/or results may be used in conference presentations nationally and/or internationally. Individual results of participants will not be published or disseminated. Authorship will be granted to individuals making a substantial contribution to the design, initiation or conduct of the trial and/or analysis and interpretation of trial data.

## Discussion

An estimated 20 million people worldwide have an AAA [48]. AAA rupture is believed to be responsible for approximately 200,000 deaths each year globally [1]. AAAs are typically identified when they are small and an effective treatment given at this stage would prevent or limit the risk of AAA rupture and the need for surgery [21, 22]. Surveys suggest that identification of effective medications to limit the need for surgery and AAA rupture is a top priority for both patients and vascular specialists [49, 50]. Despite an enormous number of pre-clinical studies and multiple clinical trials, there is no convincing evidence to recommend any drug therapy for AAA [20, 21]. Based on strong pre-clinical and human observational data, this trial will test whether metformin limits serious AAA-related events. Unlike all prior trials, MAT is powered to test the effect of metformin on AAA events.

Metformin has an established safety profile in people with diabetes [51]. Multiple previous randomised trials suggest that metformin administration is also safe in people without diabetes. The GIPS-III placebo-controlled trial for example reported similar rates of SAEs in metformin (3%) and placebo (2%) groups amongst a population who had an acute myocardial infarction but no diabetes [52, 53]. Renal function and glucose concentrations were similar in both groups [52, 53]. Another trial of 203 young women without diabetes randomised to 1500 mg of metformin or placebo daily found no excess of SAEs in the intervention group [54]. Metformin administration has now been investigated in a range of populations that do not have diabetes with excellent safety reported [52–61]. Thus, there is a strong expectation that metformin is safe to administer in people without diabetes as planned in MAT.

Several other trials investigating the efficacy of metformin in limiting AAA progression have commenced or are planned [62, 63]. A key difference in the design of MAT compared to these other trials is that the primary outcome is the rate on AAA events not AAA growth. Potential advantages of the chosen endpoint over AAA growth measurement include greater clinical relevance, easier determination and stronger subsequent implementation impact. In addition, AAA growth is difficult to model accurately and exhibits temporal and inter-patient variation [22, 64, 65]. While decisions about the requirement for AAA repair may vary between vascular surgeons, investigational sites and countries, the blinded allocation of treatment and the stratification of randomisation by site will be protected against bias from these potential issues. Furthermore, all suspected primary outcome events will be adjudicated by review of hospital notes and other relevant materials by a blinded endpoint adjudication committee comprised of experts in the management of AAA.

A number of challenges and potential limitations of the design of MAT are also noted. Firstly, the study design requires a much larger sample size than all prior AAA drug trials [20]. This requires international collaborative design and funding support from multiple bodies which is challenging to achieve particularly during the current COVID-19 pandemic. The event rate chosen for the sample size estimate is believed to be conservative but could vary from prior trials and across nations which would influence the sample needed. While the trial has been designed to include participants tolerant of metformin this may wane over time and one previous trial, which did not include a run-in phase, reported premature discontinuation of metformin in 30% of participants [66].

In conclusion, MAT is designed to be the largest clinical trial to test a medical treatment for AAA. A positive finding from MAT will identify metformin as the first AAA drug effecting at preventing AAA-related death or rupture. Since metformin is low cost, safe and available worldwide, the trial will have direct clinical implications for people with small AAAs around the world for whom no preventive therapy is currently available.

